
### Process Documentation of SMC Adaptation

The purpose of this component is to systematically capture the process of how the SMC model implemented by the Malaria Consortium and partners in West and Central African countries is adapted to the Mozambican context. Specifically, this will take into consideration the existing government health system, structures, personnel, and service delivery at different levels. In view of the current COVID-19 pandemic, all of the aforementioned activities and tools will be appropriately adapted to this outbreak context, which will constitute an additional aspect to be documented as part of the model adaptation. Previous study protocols, implementation reports, tools, and materials from other countries where the Malaria Consortium has implemented SMC will be reviewed and collated. Relevant materials will be adapted and translated for the Mozambican context. All of these adaptations will be captured using a template process documentation tool.

### Feasibility and Acceptability Assessment

A key component of investigating the feasibility and efficacy of SMC in Mozambique is understanding the views and experiences of those involved in its implementation and use.

To explore the feasibility and acceptability of implementing SMC, a qualitative assessment using key informant interviews and focus group discussions (FGDs) will be conducted. This study component will examine how SMC is viewed, experienced, and engaged with by different stakeholder groups, including policy makers, implementers, and beneficiaries.

The study population includes health workers and community volunteers who are involved in SMC implementation, caregivers of children aged 3-59 months, community members, community leaders, and key decision makers such as health officials at different levels of the health system. Purposive approaches to sampling will be adopted to include those best able to provide insight into the topic being explored and a range of views and experiences relating to SMC [36]. Participants will fall under four main groups: caregivers of children eligible for SMC; health workers and community volunteers involved in SMC delivery; community members in areas where SMC is implemented; and key informants involved in SMC implementation, program management, and policy making.

Within each participant group, participants with a range of different experiences will be identified, where possible. For example, for caregivers, efforts will be made to include participants of different genders, ages, living in more rural and urban locations; those considered more marginalized, such as adolescents, older caregivers, and people living remotely; and those with different socioeconomic status and education levels. Although we presume that most caregivers will be female, we will attempt to include male caregivers where possible and relevant. We will also aim to include those with different experiences relating to SMC, that is, those who refused and those who agreed to receive SPAQ for their children. For health workers and community-based volunteers, those of different ages and experience and seniority levels will be identified for recruitment. For community members, those with potentially different perspectives will be included, for example, village leaders, older men, older women, and younger women. For key informants, implementing partners and those from district, provincial, and national levels and with a range of different potential insights, for instance, relating to malaria prevention policy making, program management, and drug supply chain management, will be identified for recruitment. In addition to identifying participants purposively, the end-of-round approaches to sampling will be adopted, with the final sample size determined based on evidence of achieving data saturation, when additional participants do not generate new findings relating to the topic of investigation [37,38]. We estimate recruiting approximately 10-20 participants per group (Table 3) for participation in an in-depth interview. In addition, 6-12 FGDs will be conducted with approximately 6-8 participants per group.

Data will be generated through in-depth interviews and FGDs, based on topic guides, to explore views on SMC, areas relating to SMC acceptability, and reflections on the implementation experience. Topic guides will serve as prompts for the interviewer but will be flexible and participant led. In-depth interviews will aim to encourage participants to elaborate and provide in-depth accounts of their views and experiences relating to SMC, or *thick descriptions* [39], including through using nonverbal and verbal probing. Topic guides will vary the areas of focus, depending on the participant group. For example, interviews with caregivers will explore topics including general views on malaria, malaria prevention options, and SMC, as well as perceived malaria risk, perceived benefits and costs or negatives of SMC, concerns, challenges, and support. Interviews with community distributors will explore topics such as experiences administering SPAQ, how community members respond to SMC, what community distributors themselves think about the pros and cons of SMC and its appropriateness in the region, challenges, and support for engagement with it. Interviews with key informants will explore topics relating to implementation views and experiences, including reflections on the pilot implementation, the appropriateness of SMC for preventing malaria in the region and country, and challenges and opportunities for national rollout.

**Table 3 table3:** Sampling frame.

Participant group and estimated sample size		Data collection technique
**Caregivers**		
	10-20	IDI^a^
	3-6	FGD^b^
**Health workers and community-based volunteers**		
	10-12	IDI
	3-6	FGD
**Key informants or stakeholders**		
	10-12	IDI
**Community members**		
	3-6	FGD

^a^IDI: in-depth interview.

^b^FGD: focus group discussion.

FGDs can facilitate an understanding of social norms, providing access to a range of perspectives [40], and the interaction between participants [41]. FGDs will therefore enable the exploration of wider views on SMC acceptability in the communities where the pilot is implemented, as well as views regarding different malaria prevention options, decision-making processes relevant to SMC, and potential barriers and facilitators for SMC implementation. FGDs with community members and caregivers will be homogenized by gender and age to facilitate interaction among participants and the expression of norms and consensus among peers in a grouping that is sensitive to cultural norms. All interviews and FGDs will be audio recorded and then transcribed and translated verbatim. Data collection and analysis will be conducted iteratively, with data analysis beginning at the point of data generation and with participant recruitment and topic focus being adapted as data collection progresses to further test emerging concepts and potential discrepancies from majority themes [42]. Data will be analyzed thematically using coding to identify emergent patterns, concepts, and categories from participants’ accounts.

### Coverage and Quality Evaluation (End-of-Round Survey)

#### Overview

The aim of this component is to evaluate the process of SMC implementation in terms of quality, coverage, and adherence to COVID-19 safety guidelines*.* To evaluate the coverage provided in the SMC pilot, an end-of-round survey will be conducted in March 2021. The objective of the end-of-round survey is to retrospectively determine coverage by surveying caregivers of eligible children aged 3-59 months and ineligible children aged 60-119 months, as leakage into the older age group has been anecdotally observed in other SMC countries [43]. Caregivers will be asked if their children receive the full 3-day course of the SPAQ during each cycle of the SMC round. The key indicators that will be assessed will include (1) the proportion of households with eligible children visited by a community distributor, (2) the proportion of day one SPAQ administered by community distributors to eligible children (in terms of children who received day one SPAQ at least once during 2020-2021 and by monthly cycle), (3) the proportion of eligible children who received a full 3-day course of SPAQ (including day 2 and day 3 AQ, among eligible children who received day one SPAQ), (4) the proportion of SPAQ administered by community distributors by directly observed treatment (among eligible children who received day one SPAQ), and (5) the proportion of day one SPAQ received per eligible child over the course of the SMC round (including the proportion of children who received day one SPAQ during all four SMC cycles). To measure the quality of SMC coverage, the three key indicators assessed will be the correct age eligibility included, correct directly observed therapy observed, and correct dosage administered. These quality indicators are included along with the coverage indicators in an end-of-round survey tool.

#### End-of-Round Survey Study Area

This study aims to achieve a representative sample of children aged 3-119 months in households grouped within clusters identified from health facility catchment areas across the 2 intervention districts of the SMC pilot (ie, Malema and Mecuburi).

#### Study Design

For this objective, the design will be a cross-sectional cluster randomized survey to evaluate the coverage level and quality of SMC piloted in the Malema and Mecuburi districts. Households refusing to participate in the study will be replaced with the next eligible household until the estimated sample size is attained.

#### Sample Size and Technique

The end-of-round survey will use multistage random samples of households in areas covered by the Malaria Consortium’s SMC pilot and will intend to achieve a representative sample of the target population at the district level to estimate the coverage of SMC at the level of individual eligible children. The sampling protocol aims to achieve a self-weighted sample with sampling units selected with a probability proportional to size. Only at the last stage of sampling (ie, at the household level) will a constant number of eligible children (1 child per household) be selected. The survey will be powered to provide an estimate of SMC coverage for children aged 3-59 months with a margin of error of 5%, while also providing a representative sample of children aged 60-119 months. The main sampling frame for the selection process will be a list of villages. Villages will then be randomly selected using the probability proportional to size. Villages will be the primary unit of sampling through which households and eligible children will be selected randomly. This may be reviewed once the study starts if this approach is not feasible in practice. A primary caregiver in this survey refers to any individual, aged at least 18 years, with the primary responsibility of feeding and daily care of at least one child aged less than 5 years, in a household where he or she has been a resident before the start of the SMC pilot or 1 month before the last cycle of SMC. The sample size calculation was performed using Stata 16 using the *svysampsi* command, based on the following assumptions: (1) the assumed intracluster correlation is 0.2; (2) 15 eligible children per cluster (b=cluster size); (3) the (design/cluster effect) = 1 + (b − 1) intracluster correlation = 1 + (15 − 1) 0.2 = 3.8; (4) the coverage rate of SMC in children aged 0-4 years of at least 80% (and in children aged 5-9 years of at most 20%); (5) a margin of error of 5%; (6) finite population adjustment is applied (75,000); (7) nonresponse rate of 5%; and (8) assumed ratio of children aged 5-9 years to those aged 0-4 years of 0.88.

#### Sampling Procedure

The sample size calculation revealed that a sample of 1842 children was required. It was decided that the survey would include 120 clusters, each comprising 15 children (n=1800), with 60 in each of the two districts. A constant number of households (15) will be randomly sampled from these areas, with the assumption that the populations in each sampling unit were of approximately equal size. One eligible child will be sampled from each compound in the absence of a household-level sampling frame, under the assumption that households contain a similar number of eligible children. Sampling at each stage will be conducted without replacement; once a supervision area or cluster has been selected, it should no longer be eligible for further selection.

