Coverage and quality evaluation	Quantitative: end-of-round survey	Eligible children aged 3-119 months who have been a resident in the study location for a minimum of at least one month, during the SMC pilot implementation period. Survey responses will be provided by caregivers	Households with children aged 3-119 months, resident in the study location >1 month during SMC Aged 18 years or older with the primary responsibility of feeding and daily care of at least one child aged 3 months to 10 years	No one aged 18 years or older available at the time of data collection No children aged 3-119 months present Refusal to participate	1800 (54.22)

^a^SPAQ: sulfadoxine-pyrimethamine and amodiaquine.

^b^SMC: seasonal malaria chemoprevention.

^c^RDT: rapid diagnostic test.

^d^DHIS2: district health information software.

^e^SISMA: Sistema de informação em Saúde e Monitoria e Avaliação.

^f^HMIS: health management information system.

^g^N/A: not applicable.

^h^KII: key informative interview.

^i^FGD: focus group discussion.

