#### Data Analysis

Data analysis will be carried out using Stata 16. Coverage will be calculated using the proportion command. Population size weights will be applied using the svy command as appropriate for estimates of coverage indicators when it is not possible to achieve a self-weighting sample. All indicators of interest will be calculated as proportions by district and an average across both districts.

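### Taking one child per household or compound is not self-weighting unless child counts are equal; the survey names no child-count weight and defines the caregiver in two conflicting ways

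*Protocol article*

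**What the plan says.** All places are in the Protocol article, mainly under Coverage and Quality Evaluation.

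- **Aim (Sample Size and Technique).** Coverage is to be estimated for individual eligible children. "The sampling protocol aims to achieve a self-weighted sample with sampling units selected with a probability proportional to size". At the last stage only, "will a constant number of eligible children (1 child per household) be selected".
- **Unit and assumption (Sampling Procedure).** "One eligible child will be sampled from each compound in the absence of a household-level sampling frame", and this is done "under the assumption that households contain a similar number of eligible children".
- **Weights (Data Analysis of the survey).** "Population size weights will be applied using the svy command as appropriate for estimates of coverage indicators", where a self-weighting sample cannot be achieved.
- **Caregiver, in the text (Sample Size and Technique).** The respondent is an adult "with the primary responsibility of feeding and daily care of at least one child aged less than 5 years".
- **Caregiver, in Table 2 (coverage and quality row).** The respondent cares for "at least one child aged 3 months to 10 years", and any household with a child aged 3-119 months qualifies.
- **Refusals (Study Design of the survey).** "Households refusing to participate in the study will be replaced with the next eligible household until the estimated sample size is attained".

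**The concern.** A self-weighted sample gives every child the same chance of selection. With a fixed take of one per home, an only child is certain to be chosen once the home is drawn, while a child with two others in the pool has one chance in three. The plan meets this with an assumption, although the count of children is needed anyway to pick one at random. The sampled unit also changes between sections, from household to compound. A compound may hold several households, so child counts may vary more there than the stated assumption about households covers.

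The survey estimates two things this can affect: coverage at 3-59 months, and leakage to children aged 60-119 months, for whom a representative sample is intended. If either varies with the number of children in the home, the unweighted proportion does not describe the child population, and a larger sample does not help.

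The two caregiver definitions pull the older age group in different directions. Under the narrower one, a child aged 5-9 years can enter only if the respondent also cares for an under-5, and those are the homes the programme targets.

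**Working it through.** **1. The plan's own sample size.** Inputs from Sample Size and Technique: coverage 80%, margin 5 points, intracluster correlation 0.2, 15 children per cluster, finite population 75,000, nonresponse 5%, ratio of older to younger children 0.88.

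- Simple random sample: 1.96² × 0.8 × 0.2 / 0.05² = 245.9
- Finite population correction: 245.9 / (1 + 245.9/75,000) = 245.1
- Design effect 1 + 14 × 0.2 = 3.8, giving 931.2
- Nonresponse and older children: 931.2 / 0.95 × 1.88 = 1842.8

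The stated 1842 reproduces, so the sample size is not at fault. The factor 1.88 also shows that the 15 children per cluster cover both age groups.

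**2. Selection probability.** Let village v have size measure M_v and H_v homes, with 15 homes taken. A child in a home with k children in the pool has probability proportional to M_v × (15/H_v) × (1/k). If the size measure is the number of homes, M_v/H_v is constant and the result is proportional to 1/k. If it is the number of children, M_v/H_v is the village mean of k. That offsets differences between villages but not between homes within a village. In neither case is the sample self-weighting unless k is constant.

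**3. Size of the effect (assumed inputs).** The documents give no distribution of children per home and no coverage by home size. Assume 1, 2, 3 or 4 children in 40%, 35%, 20% and 5% of homes.

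- Mean of k = 0.40 + 0.70 + 0.60 + 0.20 = 1.90
- Mean of k² = 0.40 + 1.40 + 1.80 + 0.80 = 4.40
- Variance of k = 4.40 − 1.90² = 0.79

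If coverage falls by s for each extra child, the bias (unweighted minus true) is s × 0.79/1.90 = 0.416 s.

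| Fall in coverage per extra child | Unweighted | True | Bias |
|---|---|---|---|
| 0 points | 80.0% | 80.0% | 0 |
| 2 points | 80.2% | 79.4% | +0.8 |
| 5 points | 80.5% | 78.4% | +2.1 |
| 10 points | 81.0% | 76.8% | +4.2 |

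The sign reverses if larger homes are better covered.

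**4. Cost of weighting by k.** The Kish factor is 4.40/1.90² = 1.22. With 1800 interviews, 1800/1.88 = 957 are under 5, or about 8 per cluster.

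- Design effect for 8 per cluster: 1 + (7.98 − 1) × 0.2 = 2.40. Margin 1.96 × √(0.16 × 2.40/957) = 3.9 points; with weighting, 3.92 × √1.22 = 4.3 points.
- With the plan's design effect of 3.8: 4.9 points; with weighting, 4.94 × √1.22 = 5.5 points.

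The first pair uses the number of under-5s actually expected per cluster and is the more apt.

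**5. Caregiver definitions (assumed inputs).** If a share p of 5-9-year-olds live in homes without an under-5, and leakage is L1 in homes with an under-5 and L0 in homes without, applying the narrower rule shifts estimated leakage by p × (L1 − L0). With L1 = 20% (the plan's upper figure for that age group):

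- L0 = 20%: shift 0
- p = 10%, L0 = 10%: 0.10 × 10 = +1 point
- p = 40%, L0 = 5%: 0.40 × 15 = +6 points

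**The case against.** **Self-weighting is an aim, with a fallback.** The survey's Data Analysis section allows weights when self-weighting is not achieved, and an article may leave their construction to fuller documents. This has some force. But the weights named are for population size, and because equal child counts are assumed, nothing in the text would prompt a within-home weight. The article states an assumption where the correction belongs.

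**Bias is not shown.** Correct. It is zero if coverage is unrelated to home size and negative if larger homes are better covered. The survey result will also be compared with administrative and stock data (Study Tools), which is a partial check on overall coverage.

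**Homes with only 5-9-year-olds are not clearly excluded.** A reader might infer that they are. The documents do not establish it: Table 2, Study Populations and the survey's study-area section all extend to children up to 10 years or 119 months. One sentence is out of line with three other places, so this is a contradiction to reconcile.

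**Refusals.** A reader might infer that replacing refusers itself inflates coverage. It does not follow. If refusers are dropped without replacement, the estimate still describes responders only, so the same nonresponse bias remains. Stopping substitution would also cost precision: 1800 × 0.95 = 1710 completed interviews, against the 1842 × 0.95 = 1750 implied by the calculation. Only the need to count refusals stands.

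**Link to the routine-data analysis.** A reader might infer that the survey's leakage figure feeds that sensitivity analysis. The article says only that such an analysis may be considered, and does not name the survey as its source.

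**Conclusion.** The point holds in a conditional form. One child per household or compound gives unequal selection probabilities unless child counts are equal, and no weight named in the article corrects for that. Coverage and leakage can be biased if they vary with the number of children in the home: 0 to about 4 points under the assumed split and gradients, against a 5-point margin. Direction and size cannot be taken from the documents, so it would be wrong to say that coverage is overstated.

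The caregiver definitions contradict each other. If the narrower one were applied, the survey would miss its own aim for the older age group; the illustrative shift in leakage is 0 to 6 points, and it is zero if leakage is the same in both kinds of home. The finding concerns the coverage and quality objective and leaves the protective-effect comparison untouched. It is worth correcting because the remedy is cheap.

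**What to change.** 1. State one last-stage unit, household or compound, in both sections. In each sampled unit record the number of children aged 3-59 and 60-119 months.
2. Weight each child in svy by the number of children in the pool from which that child was drawn: the total count if one child is taken across both age groups, the age-specific count if the draw is made within an age group. Combine this with any population-size weight.
3. Align the caregiver definition in Sample Size and Technique with Table 2, so that care of any child aged 3-119 months qualifies.
4. Count refusals and replacements and report the response rate. Substitution may stay; this step makes nonresponse visible but does not remove its bias.

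The cost is two counts on the form, one weight variable and some wording. Precision falls by a variance factor of about 1.2 under the assumed split, which takes the under-5 margin from about 3.9 to about 4.3 points with roughly 8 under-5s per cluster, still within the 5-point target. On the plan's more cautious design effect of 3.8 it would be about 5.5 points, slightly outside the target.

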#### Study Tools

The data were collected using a questionnaire developed by the Malaria Consortium. The survey questionnaire will be translated into Portuguese and Macua languages and uploaded into the SurveyCTO software application that will enable direct, field-based computer-aided personal interview and remote capture of the data and transfer to a netbook computer.

Although the coverage surveys will be the main method to determine coverage, two additional data sources will be analyzed and compared with survey results: (1) administrative data based on SMC tally sheets completed by distributors and data compiled via summary forms and end-of-cycle reports, and (2) (coverage=doses delivered/target population) and stock consumption data (coverage=SPAQ coblister packs received before the campaign−SPAQ coblister packs left at the end/target population).

